### 10.5.3 Moderators and Subgroup Analyses

Moderators on the primary outcome will be analyzed by using an analysis of variance (ANOVA) including an interaction term of the moderator and treatment condition. This will provide information on the importance of each moderator on the treatment effect (p-values and explained variance). We will use the following baseline variables as moderators:

- Gender (male/female/other)
- Baseline migraine days (low vs. high based on median split)
- Type of migraine disease (chronic/episodic migraine)
- Duration of migraine disease (short vs. long based on median split)

In addition to that, we will display for each subgroup means and confidence intervals. These analyses will be considered explorative.

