## 2 AIM OF THE TRIAL

The aim is to evaluate the effectiveness of the M-sense Migräne app in reducing migraine days in patients with episodic migraine and chronic migraine compared to patients in a waiting list control group who have no access to the app intervention features.

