Based on this explanation we used the following assumptions as basis for the sample size estimation: reduction of migraine days in the intervention group 1.69 migraine days, and in the control group 0.42 migraine days. This resulted in a group difference of 1.27 migraine days in week 9-12 between both groups with a pooled standard deviation of 4.20. Applying a 2-sided T-test for independent groups with a power of 80% and an alpha of 5%, a total of 173 participants will be needed per group (346 participants in total for both arms). Because the primary analyses will follow the intention-to-treat (ITT) principle, all randomized patients will be included and missing data will be imputed, additional patients to compensate for dropouts have not be taken into account. The sample size was calculated with the software PASS 2008 (Version 08.0.16, Release 27.01.2011; Hintze, J. (2008), NCSS, LLC, Kaysville, Utah).

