## 9 STATISTICAL PRINCIPLES

### 9.1 CONFIDENCE INTERVALS AND P-VALUES

All confidence intervals are 95% and two-sided. All tests are two-sided and performed at a significance level of 0.05. The test statistics for the primary analyses is judged as confirmatory. All other tests are judged as explorative.

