## 10.5 ANALYSIS FOR THE EFFECTIVENESS OF THE APP

### 10.5.1 Primary analysis of the primary outcome

The analysis for the primary endpoint (migraine days week 9-12) will be conducted using an analysis of covariance (ANCOVA) with the treatment group (intervention/control) as fixed factor and baseline migraine days (during 28 days) and type of migraine disease (chronic vs. episodic migraine = stratification variable during randomization) as covariates.

The analyses will be based on the ITT population and handling drop out and missing data are defined in chapter 10.4.

From the ANCOVA model, estimated means and 95% confidence intervals, standard errors and the p-value for the group comparison will be obtained. The significance level is set at 0.05 (two-sided).

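### SAP 10.5.3 describes moderators by interaction p-values, explained variance and subgroup means, and names neither the treatment difference in each subgroup nor the difference between those effects with its uncertainty

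*Combined protocol and SAP*

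**What the plan says.** SAP section 2 sets the aim as effectiveness "in reducing migraine days in patients with episodic migraine and chronic migraine compared to patients in a waiting list control group". Randomization is stratified by migraine type (protocol 5.4, SAP 3). The confirmatory test is a single overall comparison of the two arms (SAP 8 and 9.1).

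Only SAP 10.5.3 asks whether the effect differs by type. It uses an analysis of variance with a moderator-by-treatment interaction for four baseline variables: gender, baseline migraine days (median split), migraine type, and disease duration (median split). On the read-out it says: "This will provide information on the importance of each moderator on the treatment effect (p-values and explained variance"). It adds that "we will display for each subgroup means and confidence intervals" and labels the analyses explorative. It sets no threshold for calling a moderator important or unimportant. Unlike the primary ANCOVA in 10.5.1, it names no baseline covariate.

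**The concern.** A p-value and a share of explained variance do not say how many migraine days the app saves in a given type of patient, or how far apart the two effects could plausibly be. Means per subgroup, on the plain reading, are not treatment differences either. If the interaction is poorly powered, a non-significant p with explained variance near zero is the expected result both when the effects are equal and when the app does nothing in chronic migraine.

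At stake is what the report can honestly say about chronic migraine in a study meant to support a listing for both types. If the data are too imprecise to judge, the read-out should show that. The overall confirmatory result is not affected.

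**Working it through.** **Inputs.** From SAP 7: a "group difference of 1.27 migraine days in week 9-12 between both groups", "a pooled standard deviation of 4.20", and 173 patients per group. From SAP 9.1: "All tests are two-sided and performed at a significance level of 0.05". The chronic share p appears nowhere in the documents, so it is assumed to be 5% to 50%. Data are taken as complete, with equal SD in both types unless stated.

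**The plan's own figure.** 1.69 − 0.25 × 1.69 = 1.69 − 0.42 = 1.27. Normal approximation: n = 2 × (1.960 + 0.8416)² × 4.20² / 1.27² = 171.7, so 172 per group. The exact t-test has power 79.85% at 172 and 80.08% at 173. The stated 173 reproduces.

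**Scenario A: true effect 1.27 days in episodic and 0 in chronic migraine.**

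- SE of the interaction contrast = 4.20 × √(2/173) / √(p(1−p)) = 0.452 / √(p(1−p)).
- Power comes from the noncentral t with 346 − 4 = 342 df and noncentrality 1.27/SE.
- Expected explained variance (partial eta-squared) = f²/(1 + f²), with f² = 1.27² × p(1−p) / (4 × 4.20²).
- 95% CI half-width = 1.96 × SE. For the chronic difference alone, SE = 4.20 × √(2/(173p)).

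| Chronic share | Chronic patients per arm | SE of contrast | Interaction power | Explained variance | Half-width, contrast (days) | Half-width, chronic difference (days) |
|---|---|---|---|---|---|---|
| 5% | 8.65 | 2.07 | 9% | 0.11% | 4.06 | 3.96 |
| 10% | 17.3 | 1.51 | 13% | 0.21% | 2.95 | 2.80 |
| 20% | 34.6 | 1.13 | 20% | 0.36% | 2.21 | 1.98 |
| 30% | 51.9 | 0.99 | 25% | 0.48% | 1.93 | 1.62 |
| 50% | 86.5 | 0.90 | 29% | 0.57% | 1.77 | 1.25 |

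A simulation of 20,000 trials per share gave power 13%, 21% and 24% at shares of 10%, 20% and 30%.

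**Does explained variance separate the cases?** A value below 1% means t² < 342 × 0.01/0.99 = 3.45, that is |t| < 1.86. With no moderation at all this happens in about 94% of trials. With no effect in chronic migraine it happened in 84%, 76% and 72% of simulated trials at shares of 10%, 20% and 30%. The separation is weak.

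**Scenario B: overall effect held at 1.27**, so the episodic effect is 1.27/(1−p). This gives 1.41, 1.59, 1.81 and 2.54 days at shares of 10%, 20%, 30% and 50%, with power 16%, 29%, 45% and 80%.

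**Other sensitivities, at shares of 10%, 20%, 30% and 50%.**

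- Baseline adjustment with assumed correlation 0.7 (residual SD 4.20 × √(1 − 0.49) = 3.00): 22%, 35%, 44% and 50% under A; 26%, 50%, 73% and 97.5% under B.
- Larger chronic SD (assumed 6.0): 9%, 13%, 17% and 21% under A.

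**What the proposed read-out would show.** Under scenario A at shares of 5% to 30%, a chronic interval centred on 0 has a half-width of at least 1.62 days and so contains both 0 and 1.27. It reads as inconclusive, which is the correct message. At 50% the half-width of 1.25 just excludes 1.27, so the interval becomes informative.

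**The case against.** The strongest reply is that the analysis is explorative, the primary test is untouched, and no separate claim for chronic migraine is planned. That stands, and it limits the weight of the point. A reader could also subtract the displayed arm means and combine their half-widths as √(h₁² + h₂²). So the information is inconvenient to reach rather than lost, although the result would not be baseline-adjusted. The phrase about subgroup means and intervals may even have been meant to include differences.

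The proposed intervals would be wide, and reporting them adds no power. That is true; their use is to make the imprecision visible.

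Four stronger readings are tempting, and the documents do not support them:

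- *A null effect in chronic migraine would usually be reported as an unimportant moderator.* The SAP sets no rule for that label, so this predicts how authors will behave.
- *Explained variance depends mainly on subgroup size, so a small stratum always looks unimportant.* By the formula, moving from a 5% to a 50% share multiplies f² by 0.25/0.0475 = 5.3, and doubling the difference in effects multiplies it by 4. Both matter, and even at a 50% share the value is only 0.57%. Two of the four moderators are median splits in any case.
- *The comparison will be judged by whether arm-mean intervals overlap.* No section does this; 10.5.1 uses a p-value.
- *10.5.1 omits the treatment difference.* It says "estimated means and 95% confidence intervals, standard errors and the p-value for the group comparison will be obtained", where the reference to the group comparison can be read as covering the intervals and standard errors too.

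**Conclusion.** The point holds as a reporting and model choice in an explorative analysis. At the SAP's design values, with no effect in chronic migraine and 1.27 days in episodic migraine, the interaction test has about 9% to 29% power over assumed chronic shares of 5% to 50%. Expected explained variance is 0.1% to 0.6%. The two planned measures therefore cannot tell an absent effect in chronic migraine from an imprecise estimate.

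This rests on the unknown chronic share, on holding the episodic effect at 1.27 (so that the overall effect falls to 1.27 × (1−p), for example 1.02 at 20%), and on an SD derived from 19 pilot patients. Power is clearly better with a large chronic share and the overall effect kept at 1.27, or with strong baseline adjustment. It does not follow that the trial will misreport chronic migraine, or that the primary analysis is deficient.

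**What to change.** In SAP 10.5.3, replace the ANOVA with the primary ANCOVA (treatment, baseline migraine days, migraine type), adding the moderator's main effect where it is not already in the model and the moderator-by-treatment interaction. Replace the read-out by two items:

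- the adjusted treatment difference in migraine days with 95% CI in each subgroup;
- the interaction contrast, meaning the difference between those subgroup effects, with 95% CI.

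State that a non-significant interaction is not evidence of equal effects. P-values and explained variance may stay as supplements. The analyses remain explorative and gain no confirmatory status.

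As a wording clarification only, let 10.5.1 name the adjusted between-group difference with its 95% CI explicitly.

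The cost is a few SAP sentences and a slightly extended model. No new data, patients or design changes are needed.

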#### 10.5.4 Secondary outcomes

Secondary outcomes, that are considered continuous data, will be analyzed with an ANCOVA similar to the procedure for the primary outcome. A logistic regression analysis or Chi Square Test will be used for the comparison of the two treatment conditions for the dichotomous outcome responder. The analyses of secondary outcomes are summarized in Table 2 and will be considered explorative.

#### 10.6 ANALYSIS OF ADHERENCE TO THE STUDY INTERVENTION

Adherence to the study intervention will be only analyzed in the group with M-sense Migräne because the control group has no app intervention. The adherence to the study intervention will be presented graphically over time as percentages of adherent patients per week. The analyses details are given in Table 3.

#### 10.7 ANALYSIS OF SAFETY

Based on the safety population all safety variables will be tabulated (in total and per treatment group for adverse events). We will display the number of patients with serious adverse events, suspected adverse reactions, and serious suspected adverse reactions, and the number of patients who withdraw from the study due to safety concerns. Categorical variables are reported using frequency and percentage, continuous variables are reported by giving descriptive measures (mean, standard deviation/standard error, quartiles, and range). Groups will be compared by Chi-square or Wilcoxon rank test.

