### 6.4 SAFETY MEASUREMENTS

In both groups:

- Number of patients with a serious adverse event during the first 4 weeks, second 4 weeks, and third 4 weeks, and in total.
- Counts of serious adverse events during the first 4 weeks, second 4 weeks, and third 4 weeks, and in total.

In the M-sense Migräne app group only:

- Number of patients with a suspected adverse reaction during the first 4 weeks, second 4 weeks, and third 4 weeks, and in total.
- Counts of suspected adverse reactions during the first 4 weeks, second 4 weeks, and third 4 weeks, and in total.
- Duration of suspected adverse reaction.

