## 7 SAMPLE SIZE CALCULATION

We aim to recruit 346 study participants (173 per group). The sample size estimation is based on the comparison between the group receiving the M-sense Migräne app with the group receiving the control app version for the primary outcome (migraine days in weeks 9-12), which will be treated as a continuous variable.

For the assumptions of our sample size calculation we used diary data of a project that started in July 2020, (all 19 patients included until November 11, 2020, who used the app at least over a period of 56 days after inclusion). The “Region of the Future of Digital Health” (Zukunftsregion Digitale Gesundheit) is an initiative to position Berlin as a core region for digital health in Germany by creating a digital health ecosystem forested by the Digital Healthcare Act. With the app M-sense Migräne we have been selected to participate in the “ZDG” by public tender. We think that this data can serve as suitable pilot data for the EMMA study, because M-sense Migräne is used and physicians confirm the migraine diagnosis.

Since July 2020, physicians in Berlin who are involved in the project could prescribe M-sense Migräne to their patients after migraine diagnoses and patients complete the diary and can use the interventions. During the first 4 weeks the patients had a mean of 5.63 (sd 4.20) migraine days and in the second 4 weeks (3.94 (sd 4.18), resulting in a difference of 1.69 days.

However, because this project uses a pre-post design without a 4-week baseline before intervention we had to use the first 4 weeks of the intervention as baseline, and because the project just started

in summer only 4 further weeks were available. Both aspects will result in an underestimation of the effect but support a conservative approach of the assumptions.

In addition, we assume that using the app with no app intervention in the control group can also have an impact on the primary outcome but that this is smaller than in the intervention group. We assume a reduction of 25% of the migraine days of the intervention group in the control group (=0.42 days). Since the placebo effects described in the literature for migraine prophylaxis were mainly around 20% of the effect, this seems to be reasonable conservative.

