| Number of patients with concomitant activity/activities against headache (all and specific) | daily               | week 1-4, week 5-8, week 9-12                | dichotomous | Yes, no         |                                                                | Chi             | ITT                 |
| Study dropouts                                                                              |                     | week 1-4, week 5-8, and week 9-12, week 1-12 | dichotomous | Yes, no         |                                                                | Chi             | ITT                 |
| Safety measurements                                                                  |                     |                                              |             |                 |                                                                |                             |                     |
| Counts of serious adverse events                                                            | week 4, 8, and 12   | week 1-4, week 5-8, week 9-12                | continuous  | ≥0              | higher values indicate higher number of serious adverse events | Wilcoxon rank test          | ITT                 |
| Number of patients with at least one serious adverse event                                  | week 4, 8, and 12   | week 1-4, week 5-8, week 9-12                | dichotomous | Yes, no         |                                                                | Chi             | ITT                 |

\* with treatment group (fixed factor) and respective baseline value (if applicable) as covariate

**Table 3.** Descriptive outcomes for the group with M-sense Migräne

| Outcomes                                                        | Time of measurement | Refers to...                  | Scale                                    | Possible values | Interpretation                                                        | Analysis method | Analysis population |
|-----------------------------------------------------------------|---------------------|-------------------------------|------------------------------------------|-----------------|-----------------------------------------------------------------------|-----------------|---------------------|

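### The SAP compares serious adverse events between arms by p-value alone, without a risk difference or confidence limit, and Table 2 leaves out the 12-week total

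*Combined protocol and SAP*

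**What the plan says.** SAP 6.4 defines two SAE outcomes for both arms, the number of patients affected and the number of events. Each covers the three 4-week periods and the whole 12 weeks, for example: "Counts of serious adverse events during the first 4 weeks, second 4 weeks, and third 4 weeks, and in total".

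SAP 10.7 tabulates the safety variables in the safety population, with frequencies and percentages, and adds one sentence on comparison: "Groups will be compared by Chi-square or Wilcoxon rank test".

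SAP Table 2 carries this out. The row "Number of patients with at least one serious adverse event" gets a chi-square test and the row for event counts gets a Wilcoxon test. Both rows list weeks 1-4, 5-8 and 9-12 only, and both name ITT as the population. In the same table, the row for study dropouts does include weeks 1-12.

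SAP 9.1 sets the general rule: "All tests are two-sided and performed at a significance level of 0.05". Only the primary test is confirmatory: "All other tests are judged as explorative". It also says that confidence intervals are 95% and two-sided, but no safety section asks for one. Protocol 11.10 names tabulation and descriptive measures and mentions no test.

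**The concern.** The synopsis counts safety among the secondary objectives, and the results go to the regulator. Apart from per-arm counts and percentages, the only comparative SAE result the SAP specifies is a p-value. With few events, a large p-value fits equally well with no harm and with an excess of several percentage points. The reader needs the size of excess that the data cannot rule out, and the plan does not ask for it. For the primary outcome, by contrast, SAP 10.5.1 asks for estimated means, standard errors and 95% intervals.

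The windows add to this. The 12-week total holds the most events, yet it is the one period defined in SAP 6.4 for which Table 2 lists no comparison.

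**Working it through.** **Inputs.** 173 patients per arm (SAP 7), 1:1 allocation (protocol 5.4), two-sided 5% level (SAP 9.1). The documents give no SAE rate. Protocol 8.1 says only that the intervention in an earlier study was not associated with SAEs. I therefore assume 12-week control risks of 1%, 2% and 3%, with one third of the risk in each window.

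**1. The plan's own figure.** SAP 7 assumes a "group difference of 1.27 migraine days in week 9-12 between both groups with a pooled standard deviation of 4.20". The standardised difference is 1.27/4.20 = 0.302. With 173 per arm the noncentrality is 0.302 × √(173/2) = 2.81, and the two-sided t-test has power 0.801; with 172 per arm it has 0.799. So 173 is reproduced. It concerns migraine days. No power or precision is stated for safety.

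**2. How often chi-square misses a doubling.** For a and b affected patients, n = 173 per arm:

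X² = 2n(a − b)² / [(a + b)(2n − a − b)], significant if X² > 3.84.

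Miss rate = 1 − the sum of Bin(a; 173, p₁) × Bin(b; 173, p₀) over all significant tables.

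| Assumed 12-week risk, control vs app | Missed on the total | Missed in one window | Missed in all three windows* |
|---|---|---|---|
| 1% vs 2% | 90% | 98% | 95% |
| 2% vs 4% | 82% | 93% | 81% |
| 3% vs 6% | 73% | 90% | 72% |

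*Treating the windows as independent.

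Each window alone is clearly weaker than the total. The three taken together are worse than the total at 1% and about equal to it at 2% and 3%. The main loss from windowing is therefore that the most informative comparison is not listed; combined power does not always fall.

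The result depends on the assumed rate and effect. For a tripling, the total misses 76%, 51% and 33% at control risks of 1%, 2% and 3%.

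**3. What an interval would show.** Take 5 patients with the app and 2 in the control arm.
- X² = 346 × 3² / (7 × 339) = 1.31, p = 0.25.
- Risks 2.89% and 1.16%; difference +1.73 points.
- Wilson limits: 1.24% to 6.59% (app), 0.32% to 4.12% (control).
- Newcombe lower limit: 1.73 − √[(2.89 − 1.24)² + (4.12 − 1.16)²] = −1.7.
- Newcombe upper limit: 1.73 + √[(6.59 − 2.89)² + (1.16 − 0.32)²] = +5.5.

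With no events in an arm, the Clopper-Pearson upper limit is 1 − 0.025^(1/173) = 2.1%. With 0 versus 0, the Newcombe interval is ±2.2 points.

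**4. The passages side by side.**

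| | Periods for SAEs | Population |
|---|---|---|
| SAP 6.4 | three windows and total | not stated |
| SAP 10.7 | not restricted | safety population |
| SAP Table 2 | three windows only | ITT |

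**The case against.** The case against giving this much weight has several sound parts.

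- **Counts are visible.** Numbers and percentages per arm will be tabulated, so a reader can derive the risk difference and its interval. Protocol section 9 adds listing, causality and severity assessment and three-monthly review. For a handful of events, that case-level review matters more than any test. This stands, and it is why the point is minor.
- **The tests are explorative.** A reader might infer that a non-significant result will be reported as proof of safety. The documents do not support that: they contain no such rule, and SAP 9.1 reserves confirmatory status for the primary test.
- **The total is not abandoned.** SAP 6.4 defines it and SAP 10.7 does not limit its comparison to windows. The missing row in Table 2 may be an oversight; the single-window miss rates describe Table 2 read literally.
- **Chi-square is not shown to fail.** A reader might infer from sparse cells that the test is invalid or raises false alarms. All expected counts reach 5 only with at least 10 affected patients in the period (2.9% of 346). Even so, at equal per-period risks of 0.33% to 3%, the exact error of uncorrected chi-square is 0.003 to 0.046, below 0.05 throughout. Individual p-values do depend on the test (4 versus 0 gives 0.044 by chi-square and 0.123 by Fisher), but Fisher misses more: 97%, 89% and 82% in the three doubling scenarios. Changing the test is a trade-off and does not solve the problem.
- **Low power is inherent.** The trial was sized for migraine days, and no method makes rare events informative at 346 patients. True, but an interval shows that limit, whereas a p-value hides it.

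None of this supplies the missing estimate or the missing row.

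**Conclusion.** The point holds as a minor reporting weakness. The SAP specifies no effect estimate or confidence limit for the SAE comparison, and Table 2 omits the 12-week total that SAP 6.4 defines. At assumed control risks of 1-3%, chi-square on the total misses a doubling 73-90% of the time, and in one window 90-98%. These figures rest on assumed rates, an even spread over the windows and full follow-up of 173 per arm. A broader claim, that the tests would miss most relevant harms, is not supported: at a 3% control risk a tripling is found with 67% power on the total.

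The primary result is unaffected. The disagreement between SAP 10.7 and Table 2 on the SAE population is a separate inconsistency in the same rows.

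**What to change.** In SAP 10.7 and Table 2:

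- Make the 12-week total the SAE comparison: number and percentage of patients with at least one SAE per arm, and the risk difference with a two-sided 95% interval (Newcombe or Miettinen-Nurminen). When an arm has no events, also give its Clopper-Pearson limit.
- Show weeks 1-4, 5-8 and 9-12 descriptively.
- Name one analysis population for the SAE rows, the same in both places.

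The cost is a few lines of SAP text and code, with no new data. The drawback for the sponsor is a less favourable-looking safety statement: an upper limit of around 2 percentage points would appear even with no events, and of several points with a few.
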